### Interim analyses {21b}

No interim analysis will be performed.

### Methods for additional analyses (e.g., subgroup analyses) {20b}

For sensitivity analysis, unadjusted and complete case (without imputation of missing data) analyses will additionally be carried out for primary and secondary outcomes. Potential moderators, such as individual differences in socio-demographic factors (age, sex, etc.) or vocational school-level factors (i.e., vocational sector, etc.), and potential mediators (mechanisms of action) such as self-efficacy or abstinence/reduction-related control beliefs will be explored in interaction analyses.

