### Trial design **{8}**

The current study uses a cluster-randomized controlled exploratory trial with two arms, an intervention group (IG), and a waitlist control group (CG) with pre-post assessments. All study participants will be randomly assigned to one of the two groups on the class level (Fig. 1).

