#### Secondary outcomes

A number of individual-level secondary outcome measures were selected based on their health-related relevance and associability with the conceptual intervention approach. These outcomes are as follows:
Problematic cannabis use (Severity of Dependence Scale (SDS), 5 items [26]; German version: [27])Problematic gambling (Brief Biosocial Gambling Screen (BBGS), 3 items [28])Psychological stress (Depression Anxiety Stress Scales 21 (DASS-21), subscale stress, 7 items [29]; German version: [30])Impulsivity and sensation seeking (Substance Use Risk Profile Scale (SURPS), subscales impulsivity and sensation seeking, 2 items each [31])Mindfulness skills (Child and Adolescent Mindfulness Measure (CAMM), 10 items [32])Physical activity (past month frequency of physical activity/sports, single item, self-constructed)Positive mental health (Positive Mental Health Scale (PMH), 9 items [33])Life satisfaction (L1, General Life Satisfaction Short Scale, single item [34], German version [35])General self-efficacy (Short Scale for Measuring General Self-efficacy Beliefs (ASKU), 3 items [36])Readiness and confidence to quit or reduce the use of alcohol, nicotine, cannabis, gaming, social media, and gambling (readiness/confidence ruler (10 = “not at all ready/difficult to change” to 100 = “very ready/difficult to change”) assessing readiness and confidence in quitting or reducing each behavioral outcome; based on [37])

For a list of included secondary outcomes, see Fig. 2. Additionally, we assess socio-demographic data (age, gender, migration background, socio-economic status), progress of vocational education, educational sector, and frequency of in-school education.

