#### Sample size {14}

The sample size is calculated to detect a minimum relative difference of 20% between both groups at post-assessment. This effect was based on previous studies on the effectiveness of substance use prevention programs [11, 19] and takes a clustered data structure and an intra-class correlation (ICC) of 0.032 as well as a drop-out rate of 30% on the student level into account (based on [15]). The required sample size for 80% power to detect between-group differences at the 0.05 level is 4500 students (2250 students per condition) from 225 classes.

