## Statistical methods

### Statistical methods for primary and secondary outcomes {20a}

Analyses will account for the clustering of individuals in school classes and will be reported following CONSORT standards. Trial variables will be analyzed by the intervention arm, into which participants were randomly assigned. Continuous outcomes will be reported for each trial arm using means and standard deviations, and binary outcomes will be reported for each trial arm using numbers and percentages. The main intervention effects will be tested by means of logistic or linear multi-level/random effects regression models with the levels “classes” and “individuals,” whereby group and time variables as well as the interaction term group × time are used. Primary between-group analyses will be adjusted for baseline scores of the outcome variable, relevant covariates (baseline prognostic factors that are theoretically associated with outcomes, including, but not limited to age, gender, and migration background as well as the personality traits sensation seeking and impulsiveness), and those variables used to stratify randomization.

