## Discussion

The present study aims to transfer the voluntary abstinence approach that has been established in regular schools to the vocational school setting and extends it to digital media-related addictive behaviors. This will be the first time that a prevention program for vocational schools will be developed and rigorously evaluated in a randomized study in Germany. Moreover, the scientific evaluation of a fully app-based intervention of this approach extends the literature on prevention measures based on the voluntary commitment which up to now has been mainly established in the form of the class competition “Be smart – don’t start” [17].

If the trial results suggest that the approach is feasible and effective, this could provide a much needed evidence-based, relatively low-cost, and scalable program to reduce substance use and Internet-related problems at vocational schools in Germany. All MZo materials (explanation video, app, MZo website) is designed to require minimal effort and resources for schools/teachers. The “core intervention material” is the MZo app which can be considered credible for the target group since vocational students participated in the process of conceptual development to pilot testing for usability and acceptability.

To facilitate recruitment of vocational schools, the cluster RCT design is limited to a convenience sample of vocational schools willing to participate and a pre-post design. While this approach may result in selection bias and limit conclusions regarding long-term effectiveness, we consider this approach acceptable given that the study evaluates the effectiveness of a newly developed intervention. Although the recruited sample cannot be considered representative of vocational schools in Germany, the generalizability of the results is facilitated by the inclusion of a broad range of vocational sectors (i.e., service industries, business and administrative professions as well as industrial-technical professions) within schools from three different states across Germany. Moreover, implications for practice will be gained. The study will contribute to the knowledge on how to effectively implement the MZo intervention in (vocational) schools. Finally, the inclusion of a range of potentially relevant secondary outcomes, covariates, moderators, and mediators in a reasonably large sample is expected to add to a differential understanding of the trial results.

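### Mediators are assigned to interaction analyses, which test effect modification and cannot by themselves show that self-efficacy or control beliefs carry the effect

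*Protocol article*

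**What the plan says.** The sentence at issue is in the protocol article, section 20b (additional analyses). It starts with moderators, giving socio-demographic and school-level factors as examples, and continues: "potential mediators (mechanisms of action) such as self-efficacy or abstinence/reduction-related control beliefs will be explored in interaction analyses". Both kinds of variable share one verb and one method. The bracketed gloss shows that mediator is meant in its technical sense, a variable through which the app works.

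Three other places bear on the point:

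- Section 20a has the only other interaction in the article, in the model for the main intervention effects: "whereby group and time variables as well as the interaction term group × time are used".
- Trial design (item 8) describes "a waitlist control group (CG) with pre-post assessments", so there are two measurement occasions.
- The Discussion gives the mediators a purpose: including "the inclusion of a range of potentially relevant secondary outcomes, covariates, moderators, and mediators in a reasonably large sample" is meant to help in understanding the results.

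General self-efficacy is listed under Secondary outcomes as a three-item scale. No section mentions an indirect effect or any other mediation model.

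**The concern.** Moderation and mediation are different questions. A moderator is a characteristic, normally measured at baseline, across whose levels the intervention effect differs. A mediator is changed by the intervention and passes that change on to the outcome. An arm × variable interaction addresses the first question only.

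Used alone for mediators, the named method can go wrong in two ways. It can miss a mechanism that carries the whole effect. It can also present as a mechanism a variable that the intervention never moved. What is at stake is the trial's account of how the app works, not whether it works.

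**Working it through.** The plan gives no figure on this point, so there is nothing to reproduce. The check is algebra, followed by a simulation at the trial's size.

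**1. Full mediation.** Let A be the arm, M the mediator and Y the outcome, with M = aA + e and Y = bM + u.

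- Substituting, Y = abA + be + u. The total effect is ab, and all of it is indirect.
- Given A and M, the expectation of Y is bM. In a regression of Y on A, M and A×M, the A×M coefficient is therefore 0.
- With the baseline value M0 instead, and the post-assessment value M1 = 0.5·M0 + aA + e, the expectation of Y given A and M0 is abA + 0.5b·M0. Again there is no A×M0 term.

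**2. Moderation without mediation.** Let a = 0 and Y = bM1 + cA + d·A·M0 + u.

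- The indirect effect is 0 × b = 0.
- The A×M0 coefficient is d.
- If M0 and M1 have unit variance and correlation 0.5, the A×M1 coefficient is 0.5d. For d = −0.15 this is −0.075.

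The interaction is thus zero where mediation is complete, and non-zero where there is none.

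**3. Simulation inputs.** Item 14 states: "The required sample size for 80% power to detect between-group differences at the 0.05 level is 4500 students (2250 students per condition) from 225 classes". The same section gives an intra-class correlation of 0.032 and 30% drop-out.

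- Students per class: 4500 / 225 = 20. Retained: 20 × 0.7 = 14.
- Runs: 1000 per scenario, two-sided 0.05, linear regression with class-robust standard errors.
- Path sizes a, b, c and d, in SD units, are assumptions because the document gives none.

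Three tests were compared: arm × post-assessment mediator, arm × baseline mediator, and a joint test of the two mediation paths (arm to mediator, and mediator to outcome given arm).

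| Scenario | Arm × post mediator | Arm × baseline mediator | Joint path test |
|---|---|---|---|
| Full mediation, a = 0.2, b = −0.3 (effect −0.06, all indirect) | 5.0% | 4.5% | 100% |
| Full mediation, a = 0.3, b = −0.4 (effect −0.12, all indirect) | 5.2% | 4.9% | 100% |
| Moderation only, a = 0, b = 0, c = −0.1, d = −0.15 | 53.8% | 98.7% | 0.1% |
| Moderation only, a = 0, b = −0.3, c = −0.1, d = −0.15 | 56.6% | 98.5% | 4.5% |

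The simulation standard error at 5% is √(0.05 × 0.95 / 1000) = 0.7 percentage points, so the four full-mediation results for the interaction tests cannot be told from 5%.

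**4. Can the wording be read as a mediation analysis?** Two interactions do have a place in one.

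- Group × time with the mediator as outcome estimates the path a.
- A treatment × mediator term in the outcome model lets the path b differ by arm.

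Neither yields the indirect effect, which needs both paths combined.

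**The case against.** The strongest case against the point is that one condensed sentence is being read as a model specification. It fixes no model, no time point for the mediator and no error rate. The trial is described as exploratory, and these variables are only to be explored. Since self-efficacy is a secondary outcome, a group × time model would plausibly be fitted to it anyway, and causal mediation models may include a treatment × mediator term. The details could be left to an analysis plan.

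Much of this stands. The matter is exploratory, and no single test is fixed. What does not follow is that nothing is wrong. The article does not leave the method open. It names one, and that one answers another question. An analysis plan that followed it would carry the mismatch forward.

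A reader might infer more than the document supports:

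- **That the main results are compromised.** They are not. The models in section 20a do not depend on this sentence.
- **That concurrent measurement, or conditioning on a post-randomisation variable, is a further error in the sentence.** The first comes from the two-wave design and the second from any mediator-to-outcome model. Both apply equally to the analysis proposed below, so they are limits to state.
- **That no measure of control beliefs is planned.** This cannot be said. The outcome sections refer to Fig. 2, which is not shown, and a readiness and confidence ruler is listed under Secondary outcomes.
- **That the trial's test is bound to reject at 5% whatever its size.** This holds for the linear full-mediation case, not for every mechanism.

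**Conclusion.** The concern holds in a limited form. Section 20b assigns mediators to a method that tests effect modification and, used alone, cannot show that self-efficacy or control beliefs carry the effect.

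The zero expectation is exact for a linear model with full mediation and no modification. The rejection rates illustrate the distinction at this trial's size. They rest on assumed path sizes, equal retained class sizes and no mediator–outcome confounding, so the 100% for the joint path test is not a forecast of power here, and none of the rates measures harm to this trial.

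The consequence is confined to the exploratory account of mechanism. It is worth correcting because the Discussion counts on mediators to help in understanding the results and the correction is cheap.

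**What to change.** Split the sentence in section 20b, and carry the same split into the analysis plan:

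- **Moderators:** keep interaction analyses, restricted to variables measured at baseline.
- **Mediators:** estimate the indirect effect from two models that account for class clustering. One models the mediator on arm; the other models the outcome on mediator and arm. Adjust both for baseline mediator, baseline outcome and the planned covariates. Give a confidence interval that respects clustering. A treatment × mediator term may be included as a component, but it is not the test of mediation.
- **Reporting:** label the result exploratory. State that mediator and outcome are measured at the same post-assessment, so time order cannot be established, and that the estimate assumes no unmeasured mediator–outcome confounding.

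The change uses measures the trial already plans to collect and leaves the design, sample size and the primary and secondary analyses as they are. It costs a change of wording and a little more analysis work.

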### Methods in analysis to handle protocol non-adherence and any statistical methods to handle missing data {20c}

Primary analyses will be based on the intention-to-treat population, thus including data from all participants who provide baseline data within a school class that was previously randomly assigned to one of the two trial conditions. Multiple imputation methods will be used to estimate missing data.

### Plans to give access to the full protocol, participant-level data and statistical code {31c}

Anonymized study data and statistical codes will be made available upon request given that data protection according to GDPR and ethics according to ethical approval are ensured.

### Oversight and monitoring

#### Composition of the coordinating center and trial steering committee {5d}

The coordinating center is the primary sponsor of this trial and is responsible for study supervision. The coordinating investigators at the three study sites form a steering committee for the study. They meet regularly and are responsible for the critical review of the study design, the study protocol, the data management, and all the study-related documents. The coordinating investigators provide oversight on the trial and support the study team members who conduct and provide day-to-day organizational support for the trial at each site. Furthermore, the coordinating investigators are responsible for the trial registration, revisions of the study protocol and application/amendments to the ethics committee, and scheduling of regular team meetings. All involved investigators and team members ensure compliance with the study protocol.

#### Composition of the data monitoring committee, its role, and reporting structure {21a}

A Data Monitoring Committee is not considered necessary as this is a low-risk intervention.

#### Adverse event reporting and harms {22}

Information on the occurrence of adverse events will be documented. Adverse events related to the assessment or use of the MZo app during the 2-week intervention period will be recorded by the coordinating investigator.

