Recent studies suggest that vocational students represent an important target group for prevention efforts and health promotion. In a survey including 5688 German vocational students, 40.5% of the participants reported a positive screening result for problematic alcohol use and 3.6% reported a level of cannabis use that puts them at serious risk for addiction [15]. The percentage of vocational students that reported daily smoking (41%) was 2.4 times greater than their age-matched peers in the general population. With regard to addictive behaviors such as online and offline gambling and digital media use, there are currently no data available that estimate the specific risks of vocational students. However, surveys indicate that media-related problems are particularly widespread among adolescents and young adults of typical vocational school age [6, 16].

A promising school-based prevention approach is a voluntary commitment to abstain from or reduce habitual behaviors like substance use. For example, one of the most widespread programs for the prevention of smoking in secondary schools in Germany is the smoke-free class competition “Be smart – don’t start.” At the core of the program is a joint voluntary commitment of the school class to not smoke for a period of 6 months. It focuses on influencing social norms, promoting self-regulation, and addressing social influences by deploying cognitive-behavioral intervention techniques [17]. Overall, the evidence based on process and rigorous outcome evaluations, long-term and iatrogenic effects, and cost-benefit efficiency are convincing, even in comparison with other programs (see [18]). An adaptation of this approach has also been shown to be effective in the prevention of binge drinking among older adolescents in the regular school setting in a randomized study [19]. Furthermore, the results of a recent controlled study in Germany [20] suggested that a 20-min reduction of daily social media use over a period of 2 weeks is positively associated with well-being and a healthier lifestyle among students. Specifically, the reduction in social media use not only reduced social media use intensity and the level of addictive symptoms but also the amount of daily smoked cigarettes over a period of 3 months.

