#### Criteria for discontinuing or modifying allocated interventions {11b}

Participants in the intervention group can discontinue the use of the intervention app at any time by deleting the app from their mobile devices. The intervention, i.e., the use of the app, does not require any contact with the study team.

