#### Provisions for post-trial care {30}

All participating schools are provided with contact information of the study sites and can access evidence-based information material on substance use and substance use prevention via the project website.

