### Data collection and management

#### Plans for assessment and collection of outcomes {18a}

Data will be collected class-wise in schools. The baseline assessments will take place directly before the intervention and the post-assessments at least 30 days after the end of the intervention. All measures are assessed via the online system “SoSci Survey,” program version 3.2.12 (15.02.2021). All collected data is entered using participants’ personal smartphones. If individual smartphones are unavailable or not functioning due to technical problems, the study teams will provide tablets to ensure data collection. To guarantee a smooth online data assessment, the study teams will also provide a portable LTE router for a stable Internet connection in the classroom if necessary. As for the MZo app and the online assessment portal, compatibility with current Android and iOS devices is given.

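### The operative adverse event rule covers only related events in the 2-week app period, so recorded events cannot give a two-arm comparison of intervention harm up to post-assessment

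*Protocol article*

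**What the plan says.** The section on adverse event reporting and harms {22} has two sentences. The first is general: "Information on the occurrence of adverse events will be documented". The second is the only one that says which events, in which period and by whom: "Adverse events related to the assessment or use of the MZo app during the 2-week intervention period will be recorded by the coordinating investigator". The section does not say how the two fit together, or who decides that an event is related.

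Four other places bear on this:

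- Plans for assessment and collection of outcomes {18a}: "The baseline assessments will take place directly before the intervention and the post-assessments at least 30 days after the end of the intervention".
- Explanation for the choice of comparators {6b}: control students wait about 6 weeks and get the app only once post-assessment is done.
- Criteria for discontinuing or modifying allocated interventions {11b}: students may stop by deleting the app, and "The intervention, i.e., the use of the app, does not require any contact with the study team".
- Outcomes {12} and Statistical methods {20a}: alcohol, nicotine, gaming, social media, stress, positive mental health, life satisfaction, cannabis and gambling are outcome measures. They are compared by randomised arm in multi-level models with a group-by-time term.

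**The concern.** A harms record is useful in a randomised trial when it covers the period over which effects are sought, is collected alike in both arms, and does not require a causal judgement before an event is written down. The operative sentence fixes all three points the other way. Its period ends at least 30 days before the outcomes are measured, although the Objectives section expects effects to persist beyond the challenge. Its main subject, app use, does not exist in the control arm while that arm is observed. It also admits only related events, so an unexpected reaction, or a rise in a behaviour the student did not choose to reduce, may be left out before anyone can compare arms.

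The Discussion foresees a scalable programme for vocational schools if the approach proves feasible and effective. A low adverse event count from this rule could then be cited as reassurance that it cannot give.

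**Working it through.** The protocol gives no adverse event rate, count or detection target, so there is no stated figure to reproduce. The check is a comparison of the timeline with the rule.

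**Inputs.** Recording window: 2 weeks = 14 days (section {22}). Gap from end of intervention to post-assessment: at least 30 days (section {18a}). Control waiting period: about 6 weeks = about 42 days (section {6b}).

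**Step 1: share of follow-up covered.**
- Minimum time from start of intervention to post-assessment: 14 + 30 = 44 days.
- Share covered: 14/44 = 0.318, or 32%. At least 30 days lie outside.
- Using the stated waiting period instead: 14/42 = 0.333, or 33%.

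A later post-assessment lowers the share further. This is a share of days, not of harms.

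**Step 2: does the window contain an assessment?** Baseline comes directly before the intervention, so before day 1 of the window. Post-assessment comes at least 30 days after the window closes. There are two readings:
- The 2-week limit governs both parts of the sentence. Then neither assessment lies within the period, and the words about assessment-related events capture almost nothing.
- The limit governs app use only. Then reactions to either assessment can be recorded in both arms, but they measure the burden of the questionnaire, not harm from the app.

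**Step 3: what can be compared between arms?** Before post-assessment the control arm has no app, so app-related events can occur in the intervention arm only. On the first reading, practically all recordable events come from one arm. On the second, only assessment reactions are common to both. Neither gives a two-arm comparison of intervention harm.

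**Step 4: what do the outcome models add?** They compare average change by arm, so an average worsening would show. Suppose a fraction w of students worsens by an amount d and the rest improves by e. The mean change is w·d − (1 − w)·e, which is zero when e = w·d/(1 − w). For small w, a very small improvement in the majority cancels the worsening of the minority. The proportion who worsen has to be reported separately to be seen.

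**The case against.** The strongest reply is that the first sentence of the section is unrestricted and that the second merely assigns a recorder. The word only does not appear, so total exclusion of other events is an inference. That stands, and the finding is therefore that the two sentences are unreconciled and that the only operative one is narrow.

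It can also be said that a journal article leaves the eliciting and tabulating of events to the full protocol. That stands for the method of eliciting, which is not criticised here. It does not answer the limits on relatedness and period, because the article states them.

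A reader might infer more than the documents support:

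- *Students have no way to report an event.* Section {11b} says contact is not required, not that it is impossible, and under post-trial care {30} "All participating schools are provided with contact information of the study sites".
- *Harm is not compared between arms at all.* The consumption, stress and well-being measures are collected before and after in both arms and compared by arm. The past-month outcomes also cover much of the time outside the 14 days.
- *The trial will report almost no harm.* No event or reporting rate is given. If recorded rates of 0.1% to 1% are assumed, 2250 intervention students would yield 2250 × 0.001 = 2.25 to 2250 × 0.01 = 22.5 events, so a count near zero cannot be derived.
- *The low-risk rationale contradicts the survey figures.* "A Data Monitoring Committee is not considered necessary as this is a low-risk intervention" describes the intervention, whereas "40.5% of the participants reported a positive screening result for problematic alcohol use and 3.6% reported a level of cannabis use" describes existing problems in the target population. The two are compatible.

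**Conclusion.** The concern holds in a limited form. The operative sentence restricts recording to related events in a window of about 14 of at least 44 days (32%; 33% of the 6-week waiting period). It may exclude both assessments. App-related events have no control counterpart before post-assessment, so the recorded events cannot support a two-arm statement about intervention harm. The outcome comparisons limit the damage for average effects, but not for a minority who worsen.

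This rests on reading the second sentence as the rule that staff will follow; if the first sentence governs in practice, the defect is one of wording. The 32% assumes post-assessment at the earliest permitted time. The size of any missed harm cannot be estimated from the document. The primary effectiveness analysis is not affected.

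**What to change.** 1. Reconcile the two sentences of section {22}: events reported in either arm are recorded from baseline to post-assessment, whether or not judged related, and relatedness is assessed afterwards.
2. Report by randomised arm the number and proportion of students who worsened from baseline to post-assessment on stress, positive mental health and each consumption measure. Give the class-adjusted difference with a 95% CI. Fix the amount that counts as worsening before the blinded analysts see results by arm.
3. The protocol version is dated 1 April 2022 and recruitment was expected to finish that month. Where events were already collected under the narrower rule, state that limit in the report and draw no safety conclusion from the adverse event count.

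**Cost.** A wording change, notified under section {25} if it counts as substantial, and one additional table from measures already planned in both arms. No new questionnaire items are needed; they would reach only the last classes and give uneven data. The downside is a little more analysis, and background worsening will appear in both arms, so the table must be read as a difference between arms.
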